To address these variations in the evidence, the current study examines a probiotic using a combination of strains with demonstrated efficacy in both a mouse model [23] and a human trial in postmenopausal women [19], utilises a 12-month intervention period, and employs aBMD, vBMD, and bone microstructure measurement techniques synergically. We specifically focus on early postmenopausal women (i.e., up to 8 years from menopause) to target the period of most rapid bone loss [3], examining a range of hormonal, inflammatory, and bone metabolism biomarkers, alongside changes in gut microbiota composition. The current study contributes to this emerging field by examining specific mechanistic biomarkers in early postmenopausal women.

Therefore, the primary aim of the study is to assess the effect of a probiotic containing three lactobacilli strains *Lactiplantibacillus plantarum* HEAL9 (HEAL9™), *Lactiplantibacillus plantarum* HEAL19, and *Lacticaseibacillus paracasei* 8700:2 (previously identified as *Lactobacillus paracasei* DSM 13434, *Lactobacillus plantarum* DSM 15312, and *Lactobacillus plantarum* DSM 15313) once daily for 12 months on vBMD in healthy early postmenopausal women, compared to a control group that will receive a placebo. Secondary aims are to assess changes between groups over 12 months in aBMD, gut microbiota composition, blood biomarkers (including bone metabolism and turnover markers, inflammatory markers), and dietary intake. The expected intervention effect is proposed to be mediated by beneficial changes in gut microbiota composition that stimulate bone formation, suppress osteoclast differentiation, and reduce inflammation, as well as improve markers of bone mineralisation, including calciotropic hormones and increased gut production of vitamin K_2_.

The study hypothesizes that supplementation with this specific probiotic once daily for 12 months will have more favourable effects on vBMD, aBMD, and bone metabolism, compared to the placebo. This effect is expected to be mediated by beneficial changes in gut microbiota composition (i.e., shift in bacterial diversity) and a consequent production of molecules that impact bone mineralization, calcium metabolism, osteoclastogenesis, and immune function inflammation (i.e., lower inflammatory biomarkers).

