#### 2.6.3. Blood Biomarker Measurements

Blood samples will be drawn using standard sterile IV venipuncture techniques by a trained phlebotomist. All samples will be obtained from a vein in the antecubital fossa of the arm using standard phlebotomy procedures. Plasma and serum samples will be decanted and aliquoted into de-identifiable labelled tubes and stored in a −80 °C freezer for subsequent analysis. Serum and plasma will be processed, stored, and assayed in the La Trobe Nutrition Clinical Trial Laboratory. Deidentified samples will also be sent to accredited private pathology laboratories for further analyses for the measurement of the concentrations of blood biomarkers (Time points: 0, 6, and 12 months). The analyses of serum or plasma for all other biomarkers will be conducted after data collection is complete, using standardised procedures and assays. This includes bone formation (Procollagen type 1 N propeptide (P1NP), total and undercarboxylated osteocalcin) and blood–bone resorption (Serum type I collagen cross-linked C-Telopeptide (CTx) or Tartrate-resistant acid phosphatase 5b (TRAP 5b)); osteoclast differentiation molecules osteoprotegerin (OPG) and receptor activator of nuclear factor kappa-Β ligand (RANKL); calciotropic hormones 25-hydroxy vitamin D, 1,25-hydroxy vitamin D, parathyroid hormone (PTH), and calcitonin; renal and liver function markers to assess normal function; and inflammatory markers high sensitivity C-reaction protein (hsCRP) and interleukin-6 (IL-6).

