### 2.7. Sample Size

The sample size calculation was based on the changes observed in total tibia volumetric BMD (vBMD) between the two treatment arms (statistical power 80%, probability of type I error 0.05) and is adequate to achieve a difference of 1% (standard deviation 1.78%) in a previously published study [21]. This estimation showed the need to recruit 50 study participants per treatment arm. Expecting a drop-out rate of 20% from baseline to follow-up measurements, an additional sample of 24 study participants will be recruited, thus leading to total sample size of 124 (i.e., 62 per treatment arm).

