### 2.8. Statistical Analysis

All continuous variables will be checked for the normality of their distribution. Normally distributed variables will be presented as Mean (standard deviation), while non-normally distributed ones will be presented as Median (interquartile range). General linear models (Repeated Measures Analysis of Variance) will be used to examine within-group changes in the majority of primary and secondary outcome measures across all time points (baseline, 6-, and 12-month follow-up) separately for each group (probiotic and placebo), as well as between-group differences at each time point. Within-group changes across all time points (baseline, versus post-intervention, versus follow-up) and between-group differences in each time-point will be also examined for biological sample data using the same statistical test. Appropriate corrections will be applied for post hoc multiple comparisons, while all analyses will be adjusted for potential confounding factors (e.g., age, body mass index, sunlight exposure, etc.). Correlations will also be used to explore the relationship between questionnaires and biological sample data.

Mediation analysis will also be conducted to examine the potential mediating role of changes in gut microbiota composition, and to examine the potential mediating role of other biological markers on the changes observed in BMD and bone metabolism indices. This will be based on a multiple regression model between the intervention, the outcome, and the potential mediators (e.g., a one of the mediation tests will assess the effect of the intervention on vBMD, examining the changes in serum concentrations of inflammatory markers as potential mediators of the intervention’s effect). The analysis will provide a % mediating effect, i.e., the % of the variability of the examined outcome explained by the examined mediating factors.

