All statistical analyses will be performed using the SPSS statistical analysis software version 29 for Windows. Both Per-Protocol (PP), and Intention-to-Treat (ITT) analyses will take place. Per-protocol analysis will compare treatment groups, including only those study participants who completed the treatment that was originally allocated to them. Adherence to the intervention will also be taken into consideration in the per-protocol analysis by identifying and excluding potential non-adherent study participants from the analysis. All reported *p*-values will be two-tailed, while the level of statistical significance will be set at *p* < 0.05.

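### The planned % mediating effect is defined as outcome variability explained by the mediators, which is not the share of the product's effect that runs through them

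*Protocol article*

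**What the plan says.** The hypothesis in section 1 (Introduction) has a causal second part: "This effect is expected to be mediated by beneficial changes in gut microbiota composition". Section 2.8 (Statistical Analysis) plans a mediation analysis to examine it, covering gut microbiota and other biological markers as candidate mediators, and BMD and bone metabolism indices as outcomes. On the model it says: "This will be based on a multiple regression model between the intervention, the outcome, and the potential mediators". Its worked example has vBMD as the outcome, "examining the changes in serum concentrations of inflammatory markers as potential mediators of the intervention’s effect". It then defines the result to be reported: "The analysis will provide a % mediating effect, i.e., the % of the variability of the examined outcome explained by the examined mediating factors".

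No other section restates or corrects this definition. Section 2.8 does not mention an indirect effect or its ratio to the total effect.

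**The concern.** A mediated share answers this question: of the difference the product makes to bone, how much arrives through the marker? It needs two links, product to marker (a) and marker to outcome given product (b). The indirect effect is a × b, and the proportion mediated is a × b divided by the total effect.

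The defined percentage asks how much of the person-to-person spread in the outcome the markers account for. The product-to-marker link is not needed. Any marker that tracks bone change, for whatever reason, earns a positive percentage even if the product never touched it. Several of the markers in section 2.6.3, such as bone turnover markers and calciotropic hormones, could plausibly track bone change regardless of allocation.

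At stake is the mechanistic conclusion. Ordinary correlation could be published under the label of mediation, and a real pathway could look minor.

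**Working it through.** **Plan's own figure.** Section 2.8 gives no figure for the mediating effect, so there is none to reproduce. The nearest figure is the sample size in section 2.7 ("statistical power 80%, probability of type I error 0.05"), with two-sided testing from section 2.8. With difference 1 and SD 1.78:

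2 × (1.960 + 0.842)² × 1.78² / 1² = 49.7, so 50 per arm, as stated (power 80.2%).

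This confirms that 1.78% acts as the within-arm SD of the change. The sample size is not in dispute.

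**Inputs from the document.** Total effect 1%, within-arm SD 1.78% (section 2.7), 1:1 allocation (section 2.1).

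**Assumed inputs, not in the document.** Within-arm correlation r between marker change and vBMD change, 0.3 or 0.5. Product shift k of a fully mediating marker, 1.0 or 1.5 within-arm SDs. Linear relations, no covariates.

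**Step 1: outcome variance.** Within arms 1.78² = 3.168. Between arms 0.5 × 0.5 × 1² = 0.25. Total 3.418. Treatment itself explains 0.25 / 3.418 = 7.3%.

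**Step 2: marker the product does not change (a = 0).** The variability it explains is r² × 3.168 / 3.418.
- r = 0.3: 0.09 × 3.168 / 3.418 = 8.3%
- r = 0.5: 0.25 × 3.168 / 3.418 = 23.2%

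Proportion mediated: 0 × b / 1 = 0% in both cases.

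**Step 3: marker that carries the whole effect.** If the product shifts the marker by k SD and all of the 1% passes through it, the slope is b = 1/k. The marker's variance is 1 + 0.25k² in squared SD units, so the variability explained is (1/k²)(1 + 0.25k²) / 3.418 = (1/k² + 0.25) / 3.418.
- k = 1.0: 1.25 / 3.418 = 36.6%
- k = 1.5: (0.444 + 0.25) / 3.418 = 20.3%

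Proportion mediated: k × (1/k) / 1 = 100% in both cases.

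| Marker | Percentage as defined | Proportion mediated |
|---|---|---|
| Unchanged by product, r = 0.3 | 8% | 0% |
| Unchanged by product, r = 0.5 | 23% | 0% |
| Carries whole effect, k = 1.0 | 37% | 100% |
| Carries whole effect, k = 1.5 | 20% | 100% |

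The order can reverse: the unaffected marker at r = 0.5 outscores the full mediator at k = 1.5. With the total effect fixed, the defined figure also falls as the product moves a full mediator further.

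**Step 4: does having the intervention in the regression help?** Suppose the percentage is read as the R-squared the marker adds once treatment is in the model. An unaffected marker is uncorrelated with treatment, so it still adds 8.3% or 23.2%. A full mediator adds 36.6 − 7.3 = 29.3% at k = 1.0 and 20.3 − 7.3 = 13.0% at k = 1.5. This reading does not give the mediated share either.

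**Step 5: at the trial's size.** In simulations with 50 per arm (4,000 runs each), the unaffected marker averaged about 9% at r = 0.3 and 23% at r = 0.5. Its coefficient was significant in 86% and essentially 100% of runs. The average indirect effect was zero to within simulation error.

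**The case against.** The strongest reply is that the definition is a loose gloss on a sound intention. The regression includes the intervention, and the example speaks of mediators of the intervention's effect, so the analysts may mean to fit a proper mediation model. Section 2.8 also plans between-group comparisons of the biological sample data, so a marker that did not move would appear beside a null group comparison.

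Both points are fair. They limit the claim to what could be reported, and to the percentage taken alone. They do not rescue it: if proper mediation is intended, the stated definition contradicts the intention, and a null comparison elsewhere leaves the reported percentage as it is. Nor is this a detail left to a fuller plan, since the article states the definition outright.

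Three stronger readings are tempting but not supported:
- **Timing.** A reader might infer that marker change and bone change are taken over the same 0 to 12 months, leaving direction open. Section 2.8 gives no interval for the mediation model. The baseline-to-12-month change in section 2.6.2 describes the microbiome outcome, and the interval may be set in a fuller plan.
- **Weight.** A reader might treat the mediation result as a main objective. Mediation is part of the hypothesis, but section 1 does not list a mediation test among its primary or secondary aims.
- **Certainty.** A reader might conclude that correlations will be credited to the product. Given the planned group comparisons, only the possibility is supported.

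**Conclusion.** The definition in section 2.8 is wrong as written. It names a variance-explained quantity and labels it a mediating effect. The sizes in the table rest on assumed correlations and shifts, and would change with other values or with covariates in the model. The direction does not depend on the particular values: any nonzero marker-outcome correlation gives a positive percentage when nothing is mediated.

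The consequence is confined to the mechanistic analysis, and the correction should be made before results are known. The primary between-group vBMD comparison and the sample size stand.

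**What to change.** Replace the definition of the percentage in section 2.8 with wording such as:

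> The indirect effect (intervention-to-mediator path times mediator-to-outcome path, the latter adjusted for intervention) will be reported with a bootstrap 95% CI, together with the proportion mediated (indirect effect divided by total effect) and its CI. The proportion will be interpreted with caution when the total effect is close to zero.

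Apply it to each BMD and bone metabolism outcome and to each prespecified scalar mediator. Microbiota composition has several components in section 2.6.2, so the scalar summaries used as mediators need naming.

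No rule that suppresses the proportion unless the total effect is significant is needed. At the planned 80% power, about 20% of trials with the planned effect would then report nothing.

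Using the 0 to 6 month mediator change can be offered as an optional sensitivity analysis, since blood and stool are collected at 6 months. It should not be a required rule: HR-pQCT is done only at 0 and 12 months, so the outcome change still includes the first six months.

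Cost: no new data, slightly more analysis work, and a wide interval for the proportion mediated. Section 3 says the study is ongoing with no results to report, so the change can still be made in advance.

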## 3. Results

The study remains ongoing, and as such, results are not yet available to be reported as part of this study protocol paper.

## 4. Discussion

This study aims to assess the effectiveness of gut microbiota modulation on bone mineral density and bone microstructure in early postmenopausal women compared to placebo. Preliminary mouse model results demonstrated that probiotics improve bone density [35,36], but translation in human clinical trials has produced inconclusive results. Of the five randomized clinical trials that measured aBMD at lumbar spine, total hip, and/or femoral neck, only one reported improvement at more than one site [25]. Jansson and colleagues (2019) reported improvements in spine but not femoral neck, and no differences in total hip [19], whereas Takimoto and colleagues (2018) reported improvements at hip, but no differences in spine [26]. Nilsson and colleagues (2018) reported no differences in aBMD at either lumbar spine or total hip, but did report differences in vBMD (describing bone geometry and structure) favouring the probiotic intervention group [21]. Indeed, only one of the published trials [19] has been adequately powered to demonstrate aBMD differences, which may account for the inconsistency in results. Furthermore, two [24,26] trials had sample sizes (*n* = 76 and *n* = 50, respectively) powered to detect changes in specific blood biomarkers rather than BMD. One trial [26] provided a power calculation, but did not specify which outcome measure was used to determine effect size. This indicates that adequately powered studies combined with appropriately sensitive measurement techniques are required to better elucidate the effect of probiotics on bone density in humans.

In addition to adequately powered trials, sufficient intervention duration is required to detect changes in bone mineral density [37]. Two [24,26] of the five reported trials had an intervention duration of 6 months, which may be insufficient to detect change in aBMD. Intention to treat analysis was used in both analyses due to dropouts, further indicating that sample size and short duration may be responsible for no differences detected between groups. The current study is a 12-month intervention, and has a sample size of *n* = 124.

Jansson and colleagues (2018) were the only authors to identify years from menopause as part of their inclusion criteria (up to 12 years from menopause) [19]. Other authors only identified postmenopausal women and specified ages ranges for inclusion (for example, 50–72 years or 60–85 years). The period immediately following menopause has been identified as the time of greatest bone loss [4], which accounts for the higher prevalence of osteoporosis in women. This presents a novel opportunity to specifically target this timeframe for intervention. Indeed, Jansson and colleagues demonstrated that when time from menopause was limited to 12 years in the inclusion criteria, the intervention group showed less aBMD loss at lumbar spine compared to placebo. When a subgroup analysis limited year from menopause to 6 years, the probiotic group experienced less than 0.2% mean aBMD loss, whereas the placebo group reported 1.2% mean aBMD loss (*p* = 0.016). Interestingly, participants that were more than 6 years from menopause in the probiotic group experienced an improvement of 0.2% mean aBMD. This might indicate that benefits of probiotic intervention may have a role to play in the retention or improvement of bone density regardless of years from menopause. Nevertheless, the current study has limited years from menopause to 8 years, but also included a general age range (45–65 years) to further elucidate this phenomenon.

The strengths of the current study protocol are: the inclusion criteria targeting women with no more than eight years from menopause; strict exclusion criteria, such as limiting years from menopause; robust study design using novel and highly sensitive measurement techniques such as BMD, through HR-pQCT in addition to DXA, well-established microbial analysis techniques, and the inclusion of key biomarkers for mechanistic examination of bone density changes; and an a priori analysis plan. A limitation of the study is that given we are recruiting from a healthy population, the cohort will likely have a healthy user bias and may not be applicable to other populations such as those with a higher BMI, women more than eight years from menopause, or men. Furthermore, some self-reported measures may be subject to recall bias, such as dietary intake, physical activity, and years from menopause, as these are unable to be objectively evaluated. However, these limitations are present in all self-reported measures and are not unique to this trial. Limitations of the nutrient data have been mitigated by including two rather than one reported measure. All questionnaires will be completed during study visits, and participants have the capacity to clarify questions to avoid misunderstanding, limiting the potential for incorrect data being reported for physical activity and other measures. Due to the ad hoc nature of menstruation during menopause, the exact date of cessation may not always be able to be determined. Therefore, the appropriate year of cessation will be determined to be sufficient to classify eligible women as ‘postmenopausal’.

Reducing the burden of fragility fractures later in life would improve quality of life. The International Osteoporosis Foundation highlights the need to prioritize prevention as a key strategy for managing fragility fractures [38]. The findings of this study have the potential to facilitate the retention and potential improvement of BMD during a critical period of bone loss for postmenopausal women whilst elucidating mechanistic pathways of action for gut microbiota modulation.

## Figures and Tables

**Figure 1 nutrients-16-01150-f001:**
[figure not shown]
Flowchart of recruitment and enrolment process.

**Table 1 nutrients-16-01150-t001:** Overview of study data collection and timepoints.

	Screening Phase	Timepoint 0	Timepoint +6 Months	Timepoint +12 Months
Screening				
Informed consent	x	x		
Inclusion/exclusion criteria	x			
DEXA (spine or total hip)	x			
Data Collection				
Informed consent	x			
Bone density measurements				
DEXA (spine, total hip, femoral neck, forearm), QUS		x	x	x
HR-pQCT (tibia, radius)		x		x
Stool sample collection and storage (−20 °C)		x	x	x
Blood collection, processing, and storage (−80 °C)		x	x	x
Body composition				
DEXA (whole body), BIA		x	x	x
Nutritional Intake				
3-day food diary, FFQ		x	x	x
Questionnaires				
Physical activity (AAQ), Sun exposure, Quality of Life, Supplement use		x	x	x
Socio-demographics, FRAX		x		

DEXA—Dual energy X-ray absorptiometry, QUS—Quantitative Ultrasound, HR-pQCT—High Resolution peripheral Quantitative Computed Tomography, BIA—Bioimpedance Analysis, FFQ—Food Frequency Questionnaire, AAQ—Active Australia Questionnaire, FRAX—Fracture Risk Assessment Tool.

## Data Availability

The data presented in this study are available on request from the corresponding author. The data are not publicly available due to privacy restrictions and conditions of ethical approval.
